### Outcome measures

Outcome measures will be investigated via questionnaires at baseline and at 3, 6, and 12 months after enrollment. The primary outcomes will be: (1) prolonged abstinence (not smoked more than five cigarettes in the last 8 weeks) and (2) 4-week point prevalence of smoking abstinence. Secondary outcomes will be: (3) 7-day point prevalence of smoking abstinence; (4) mean number of quit attempts since taking part in the study; (5) number of uses of other smoking cessation services since first invitation to the study, e.g., calling help line; and (6) number of cigarettes smoked weekly if still smoking.

### Intervention group

The intervention will consist of a 12-week automated mHealth program with a total of 121 text messages. The program starts with two to four messages per day the first 2 weeks. In week 3, the participants will receive two messages per day. The number of messages per day will be reduced to one during weeks 4–7 and in weeks 8–12, a total of five to six messages per week. The intervention is based on a similar program developed for an adult target group [20]. The intervention was developed using formative methods, including focus groups with university students, an expert panel with university students and professionals, and behavior-change technique analysis [21]. The content of the text messages will include information about the health risks of smoking, tips on behavior-change strategies, and activities. The intervention included the following elements: making a public declaration about quitting, encouraging asking for support from family and friends, distraction techniques and tips to avoid weight gain, tips to cope with cravings and to avoid smoking triggers, and how to distract one’s mind from smoking.

### Control group

The control group will be offered treatment as usual. High-school pupils in Sweden can turn to school-based health centers, including nurses and counselors. The school health centers do offer smoking cessation support. Participants in the control group will be informed via a text message that they have been allocated to the control group. The text message will include information on where they can gain smoking cessation support, i.e., the national smoking cessation help line offering smoking cessation support to youth. No additional prompts, reminders, or information will be given to the control group during the study.

### Randomization

Participants will be randomized into two groups; one group will receive the novel intervention and the other will be referred to treatment as usual. Each participant will be allocated a number (1 or 2) with equal probability using Java’s built-in random number generator (java.util.Random). Randomization is thus fully computerized, does not use any strata or blocks, and cannot be subverted, because this and all subsequent study processes are fully automated. A runs test will be performed to test if the final allocation sequence can be considered to have been generated from a random process. The participants will know that they have been randomized to either the intervention group or the control group.

The risk of contamination between the intervention and control group is present in almost all trials of eHealth interventions as information is easily shared among participants and no restrictions can be made to make certain that only the intervention group has access to the intervention. In some cases cluster randomization may reduce the risk; however, it may also induce overconfidence that the risk has been entirely removed. Pupils attending high school in Sweden are for administrative reasons subdivided into something that resembles a traditional school class; however, pupils are mixed across classes and schools when attending courses. There is, therefore, no logical unit that shields or reduces interaction among pupils. Furthermore, with the growth of interaction among young adults using social platforms there is no longer a geographical limitation that could be used for clustering. Clustering would, therefore, in this case only accomplish a false sense of bias reduction. Analysis by treatment allocated disregarding potential contamination may lead to underestimation and, therefore, we will conduct a sensitivity analysis taking into account hypothesized probabilities of contamination rates at 5, 10, 15 and 20% (i.e., the probability that a control group participant had access to the intervention).

### Participants and procedure

Participants will be recruited through advertisements in high schools in Sweden. High school in Sweden is a free and voluntary level of education after primary school. The majority of pupils attending high school in Sweden are between 16 and 19 years of age. Inclusion criteria will be high-school pupils who are daily or weekly smokers, are willing to attempt to quit smoking, and own a mobile phone. A flowchart of the recruitment procedure for the study is presented in Fig. 1 and a Standard Protocol Items: Recommendations for Interventional Trials (SPIRIT) Figure is presented in Fig. 2.

**Fig. 1 Fig1:**
[figure not shown]
Consolidated Standards of Reporting Trials (CONSORT) flowchart

**Fig. 2 Fig2:**
[figure not shown]
Standard Protocol Items: Recommendations for Interventional Trials (SPIRIT) Figure

School principals will be contacted via e-mail and invited to take part in the study. Recruitment will last for 6 months and be executed by paper advertising (posters and leaflets), digital advertising (e-mail, school website, or app if applicable), and by school staff (teachers, mentors, and/or school health centers). Pupils will register their interest by sending a text message to a dedicated telephone number (included in all information materials). Informed consent and the baseline questionnaire will be completed on their mobile phone. After completing the baseline questionnaire, participants will immediately be randomized to the intervention group or the control group. A text message will be sent to each participant to inform them to which group they have allocated.

All participants will be sent a follow-up questionnaire via a text message (with a link to the questionnaire) at 3, 6, and 12 months after enrollment (3-month interval will be primary outcome). Three reminders, 2 days apart, will be sent to non-responders, also via text message. In addition, participants who still do not respond will be telephoned every second day, with a maximum of three phone calls. These phone calls will only include two questions investigating the primary outcomes (prolonged abstinence and 4-week point prevalence of smoking abstinence).

### Baseline questionnaire

The baseline questionnaire will include a total of 14 items investigating (1) number of year(s) of smoking, (2) frequency of using snuff, (3–8) Fagerström’s Nicotine Dependence Scale, (9) readiness to quit within the next 4 weeks, (10) number of previous quit attempts, (11) previous use of other smoking cessation aids, (12) previous support from smoking cessation specialist, (13) how they found out about the program, and (14) gender.

### Follow-up questionnaire

The follow-up questionnaire will include seven questions investigating the primary and secondary outcomes: (1) prolonged abstinence (not smoked more than five cigarettes in the last 8 weeks at the 3-month follow-up; 5 months at the 6-month follow-up; and 11 months at the 12-month follow-up), (2) 4-week point prevalence of smoking abstinence, (3) 7-day point prevalence of smoking abstinence, (4) numbers of cigarettes smoked weekly if still smoking, (5) mean number of quit attempts since taking part in the study, (6) number of uses of other smoking cessation services since first invitation to the study, e.g., calling help line, and (7) frequency of using snuff.

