### Aim and hypotheses

The study aims to evaluate the effectiveness of a newly developed mHealth intervention targeting smoking among high-school pupils. The primary hypothesis is that participants in the intervention group will report significantly higher cessation rates (measured by the primary outcome measures) at follow-up compared with participants in the control group. Secondary hypotheses are that the intervention group will report significantly higher rates of 7-day point prevalence of smoking abstinence, higher mean number of quit attempts since taking part in the study, fewer number of uses of other smoking cessation services since first invitation to the study, and lower numbers of cigarettes smoked weekly if still smoking at follow-up, compared with the control group. These hypotheses are proposed at 3, 6, and 12 months’ follow-up.

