### Data analysis

The data analysis will conform to a pre-specified statistical analysis plan. The analyses will start after collection of the 3-month follow-up data. There will be no interim analyses or stopping rules. Following the intention-to-treat analysis strategy, all analyses will include all participants with follow-up data in their groups as randomized, and sensitivity analyses will include all randomized participants to explore different assumptions about any missing data. Descriptive analyses will include summary tables (descriptive statistics and/or frequency tables) for baseline and follow-up variables as appropriate. A flowchart of recruitment of participants will be generated, including, e.g., the number of students screened and the number included in the primary and secondary analyses.

The binary outcomes of self-reported prolonged abstinence, 4-week prevalence of complete smoking cessation, and 7-day point prevalence of smoking abstinence will be analyzed by logistic regression and the results presented as odds ratios and 95% confidence intervals (CIs). Number of quit attempts and number of uses of other smoking cessation services will be analyzed by negative binomial regression and the results presented as ratios of means (95% CI). Number of cigarettes smoked weekly will be analyzed by logarithmic transformation and linear regression and the results presented as the ratio of geometric means (95% CI). All regression analyses will be adjusted for the following baseline variables: gender, duration of smoking, average number of cigarettes smoked weekly, severity of dependence as measured by Fagerström’s Nicotine Dependence Scale, and amount of snuff used at baseline. Effect modification analyses will be performed for the two primary outcomes and the following potential effect modifiers measured at baseline: gender, average number of cigarettes smoked weekly, amount of snuff used weekly, and severity of dependence. Each effect modification analysis will be performed by comparing adjusted logistic regression models, excluding and including the interaction parameter using the likelihood ratio test.

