A sensitivity analysis will explore the effects of departures from the missing-at-random (MAR) assumption in the main analysis. We will use data on the number of follow-up texts and phone calls needed before an individual responded to explore the plausibility of the MAR assumption by exploring the association between quitting and the number of follow-up attempts needed.

All tests will be performed two-sided with a 5% level of significance.

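### At 6 and 12 months, prolonged abstinence rests on a single 5- or 11-month recall, so a pupil's own earlier report of failure can be overridden or left out of the main analysis (the 3-month primary result is not affected)

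*Protocol article*

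**What the plan says.** - **Definition by wave.** Protocol, Follow-up questionnaire: item 1 is prolonged abstinence, a ceiling of five cigarettes over a look-back that lengthens by wave. It is 8 weeks for the first follow-up, then "5 months at the 6-month follow-up; and 11 months at the 12-month follow-up". Each wave has one such item.
- **General definition.** Outcome measures gives "prolonged abstinence (not smoked more than five cigarettes in the last 8 weeks" and names no wave.
- **Time points.** Participants and procedure (the text after Fig. 2) sends questionnaires "at 3, 6, and 12 months after enrollment (3-month interval will be primary outcome". Aim and hypotheses adds: "These hypotheses are proposed at 3, 6, and 12 months’ follow-up".
- **Analysis set.** Data analysis sets the main rule: "all analyses will include all participants with follow-up data in their groups as randomized". Pupils without such data enter only a second tier of work, where "sensitivity analyses will include all randomized participants to explore different assumptions about any missing data". Regressions are adjusted for baseline variables.
- **Missing data.** A sensitivity analysis examines "departures from the missing-at-random (MAR) assumption in the main analysis", and the number of contact attempts is used to judge whether that assumption is plausible.

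Nothing in the article links a pupil's answers across waves or says which answer prevails when two conflict. Data analysis refers to a pre-specified statistical analysis plan, which is not shown.

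**The concern.** The three recall periods are nested, and the criterion is a ceiling on a count. Exceeding five cigarettes in an inner period means exceeding five in any period that contains it. A failure reported at 3 months therefore settles the 6- and 12-month outcomes, and a failure reported at 6 months settles the 12-month outcome.

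Scoring each wave from its own item ignores this in two ways:

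1. A pupil who failed at 3 months, quit in month 6 and answers yes to the 11-month question at month 12 is a success, against a report given much nearer the time.
2. A pupil who failed at 3 months and is then lost has no later answer and leaves the main analysis, although the outcome is already determined.

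The Abstract and Discussion give long-term effect as a reason for the trial, and the 6- and 12-month results are what address it. The control arm is expected to have more 3-month failures, so even an equal rate of false recall adds more false successes there and pulls the odds ratio toward 1.

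**Working it through.** **Inputs from the protocol.** Recall windows of 8 weeks, 5 months and 11 months (Follow-up questionnaire). Planning rates 25.9% and 14.6%, 195 per group, 30% attrition, 279 per group (Power calculation). Up to three reminders and three calls, two days apart (Participants and procedure).

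**Inputs assumed.** The share *s* of 3-month abstainers who stay abstinent, the share *f* of 3-month failures who later answer yes (equal in both arms), and the share *r* of later losses who had answered at 3 months. The protocol gives none of these, so ranges are shown. The planning rates are taken as the 3-month rates.

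**1. The plan's own figure.** 195 / 0.70 = 278.6, so 279 per group and 558 in total, as stated. The 195 is reproduced by the unpooled normal approximation without a continuity correction (194.6). The correction that the text names is a separate matter. Nothing below changes the sample size.

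**2. Nesting of the windows** (month = 30.44 days, days from enrollment).

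| Item | Nominal window |
|---|---|
| 3 months | 91.3 − 56 = day 35 to day 91 |
| 6 months | day 30 to day 183 |
| 12 months | day 30 to day 365 |

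The 3-month window lies inside both later ones, and the 6-month window lies inside the 12-month one. The 3-month report covers 8 of 21.7 weeks (37%) of the 6-month window and 8 of 47.8 weeks (17%) of the 12-month window.

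**3. False successes.** Observed later rate = s·p + f·(1 − p), with p = 0.259 or 0.146.

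For s = 0.5, f = 5%:
- Intervention: 0.1295 + 0.05 × 0.741 = 0.1666.
- Control: 0.073 + 0.05 × 0.854 = 0.1157.
- Odds ratio: (0.1666/0.8334) / (0.1157/0.8843) = 1.53.

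| f | Rates, s = 0.5 | OR, s = 0.5 | OR, s = 1 |
|---|---|---|---|
| 0 | 13.0% vs 7.3% | 1.89 | 2.04 |
| 1% | 13.7% vs 8.2% | 1.79 | 1.99 |
| 2% | 14.4% vs 9.0% | 1.70 | 1.94 |
| 5% | 16.7% vs 11.6% | 1.53 | 1.81 |

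At s = 0.5 and f = 5%, the pupil's own 3-month report contradicts 0.05 × 0.741 / 0.1666 = 22% of intervention successes and 0.05 × 0.854 / 0.1157 = 37% of control successes.

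**4. Known failures left out of the main analysis.** Later losses are 0.30 × 279 = 83.7 per arm. Known failures among them = 83.7 × r × (1 − p).

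| r | Intervention | Control |
|---|---|---|
| 50% | 31 | 36 |
| 100% | 62 | 71 |

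**5. Effect of leaving them out** (s = 0.5, no false recall). If loss is unrelated to 3-month status, the rates are unbiased and only information is lost. If 90% of 3-month abstainers answer later and overall response is 70%, the observed rates are 0.259 × 0.5 × 0.9 / 0.7 = 16.7% and 0.146 × 0.5 × 0.9 / 0.7 = 9.4%, against 13.0% and 7.3%. Adjustment for baseline variables does not use 3-month status directly.

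**6. Why filling in failures alone is no remedy.** Suppose everyone answered at 3 months and later response is 70% regardless of status. Adding only the known failures gives 0.0907 / (0.1813 + 0.741) = 9.8% and 0.0511 / (0.1022 + 0.854) = 5.3%. Both fall below the assumed 13.0% and 7.3%.

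**The case against.** **The analysis plan may already deal with this.** The article lists questionnaire items. It does not say that earlier answers may not be used, and a rule for conflicting answers could sit in the unseen plan. That stands as a limit. What the article does fix is a single item per wave, analysed as self-report among those with follow-up data, and followed literally this has the consequences described.

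**Lost pupils do not vanish.** A reader might infer that known failures disappear from every analysis. They do not, because the planned sensitivity analyses include all randomized pupils. The article also does not say whether having follow-up data is judged wave by wave. Still, a pupil without a 6-month answer has no 6-month outcome unless earlier reports are used.

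**The main result is untouched.** A reader might infer that the primary comparison is compromised. It is not: 3 months is the primary time point, and its 8-week item has no earlier follow-up report to conflict with.

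**The direction is not a spurious benefit.** A reader might infer that false recall manufactures an effect. Equal shares in both arms attenuate the odds ratio. Participants know their allocation, so equality is not assured, but the documents give no basis for a difference in either direction.

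**Nesting is nominal.** Reminders and calls could add about 3 × 2 + 3 × 2 = 12 days. If recall runs from the answer date, a late 6- or 12-month window starts near day 42, and about 7 days of an on-time 3-month window fall outside it. If the 8 weeks in Outcome measures applied at every wave, the 6-month window would start near day 127 and there would be no overlap. Both limits stand, and the fix allows for them.

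**Conclusion.** The point holds for the 6- and 12-month prolonged abstinence results, provided the lengthening windows in Follow-up questionnaire are the intended definition. Under them, an earlier reported failure nominally determines the later outcome. The plan as written can count such a pupil as a success, or leave the pupil out of the main analysis if lost.

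The size cannot be derived from the documents. With half of 3-month abstainers staying abstinent, 1%, 2% or 5% false later answers move the odds ratio from 1.89 to about 1.79, 1.70 or 1.53. If all stay abstinent, the move at 5% is from 2.04 to 1.81. These are illustrations, and no single value should be read as the expected bias. The 31–62 intervention and 36–71 control failures dropped rest on 30% loss and on 50% to 100% of those lost having answered at 3 months. Leaving them out costs information, and it biases the rates only if loss depends on earlier status.

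This is worth correcting before the 6-month data are analysed. It does not undermine the primary analysis or the sample size.

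**What to change.** 1. Reconcile Outcome measures with Follow-up questionnaire, stating one prolonged abstinence definition for each wave.
2. If the lengthening windows stand, define 6- and 12-month success as meeting that wave's item and having no reported failure in an earlier window that it contains. Anchor windows to the scheduled date, or allow explicitly for late answers.
3. Handle later missing outcomes with a model or multiple imputation that uses arm and earlier abstinence status. Earlier failures are set to failure and earlier abstainers are imputed. Do not fill in failures alone.
4. Report the single-item result as a sensitivity analysis.

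**Cost.** This is a derivation rule on data already being collected, with no new contact and no change in sample size. Reported long-term abstinence rates will be lower, and there is some extra analysis. Pupils who skipped an earlier wave face fewer checks, so the definition depends partly on response pattern. Earlier-wave response should therefore be reported by arm.

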### Power calculation

The power calculation is based on our earlier research [20], where 25.9% reported prolonged abstinence in the intervention group and 14.6% in the control group, i.e., an 11.3% difference between the two groups. To achieve 80% power with a significance level of 0.05 (two-sided) and correction for continuity, a sample size of 195 persons is needed in each group. If there is 30% attrition in the follow-up measurements, the number needed in each group is 279, with a total required sample size of 558.

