In our previous research, we developed an mHealth intervention, NEXit, targeting smoking among university students. NEXit was developed by our research group, using formative research methods (for more details [19]). The text messages in the main NEXit study were developed based on existing evidence-based practice, expert guidance, and official smoking cessation manuals recommended in Sweden. Key elements from previous text- and Internet-based interventions were also included, e.g., problem-solving tips and distraction techniques. The effectiveness of the main NEXit intervention was evaluated in a two-arm randomized controlled trial (RCT) including 1590 participants of between 21 and 30 years of age. The trial showed a significant difference between the intervention group (25.9%) and the control group (delayed intervention) (14.6%) on 8-week prolonged abstinence. For 4-week point prevalence of complete cessation, the numbers were 20.6 and 14.2%, respectively. Students who received the intervention were almost twice as likely to quit smoking than students in the control group [20].

This article presents the study protocol of a RCT testing the effectiveness of an mHealth intervention targeting smoking among high-school pupils in Sweden.

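### The stated 80% power makes no allowance for contamination, which the protocol says it cannot prevent; the figure should be made conditional

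*Protocol article*

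**What the plan says.** The sizing takes its rates from the group's earlier trial, "where 25.9% reported prolonged abstinence in the intervention group and 14.6% in the control group, i.e., an 11.3% difference between the two groups". From these it concludes: "To achieve 80% power with a significance level of 0.05 (two-sided) and correction for continuity, a sample size of 195 persons is needed in each" of the two arms. Allowing for 30% attrition, this becomes 279 per group and 558 in total. No other allowance is made.

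The Randomization section explains why individual randomization is kept. It describes contamination as a feature of nearly all eHealth trials, says access to the programme cannot be confined to one arm, and argues that clustering would not solve this. It then concedes: "Analysis by treatment allocated disregarding potential contamination may lead to underestimation". Its response is a sensitivity analysis at "hypothesized probabilities of contamination rates at 5, 10, 15 and 20% (i.e., the probability that a control group participant had access to the intervention").

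The Data analysis section keeps participants in their groups as randomized and tests two-sided at 5%. The Background section describes the source of the 14.6%: "the control group (delayed intervention) (14.6%) on 8-week prolonged abstinence".

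**The concern.** The two sections do not fit together. One says that the as-randomized contrast may be diluted by a process that cannot be prevented. The other powers that contrast as if it were undiluted and states 80% without condition.

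The planned sensitivity analysis helps to interpret the estimate afterwards. It does not restore the power of the primary test, which is run on whatever contrast remains. If dilution occurs, a reader told that the trial had 80% power will give a null result more weight than it deserves.

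**Working it through.** **Inputs from the protocol article.** Intervention rate p1 = 0.259 and control rate p2 = 0.146 (Power calculation); two-sided 5%, so z = 1.960; 80% power, so z = 0.842; equal allocation (Design); 195 analysed per group; contamination rates q = 0.05, 0.10, 0.15, 0.20 (Randomization).

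**Inputs assumed, because the article does not give them.**
- The share f of the intervention effect gained by a control with access. I use f = 1 (full effect) and f = 0.5.
- Controls without the added access quit at 14.6%, so q is contamination beyond any already in that rate.

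**Step 1: reproduce 195.** With unpooled variance:

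n = (1.960 + 0.842)² × [0.259 × 0.741 + 0.146 × 0.854] / 0.113² = 7.849 × 0.3166 / 0.01277 = 194.6, so 195.

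The pooled-variance formula gives 198. Attrition: 195 / 0.70 = 278.6, so 279 per group and 558 in total. These match the article, but no continuity correction has been applied.

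**Step 2: apply the stated correction.** 

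n′ = (n/4) × [1 + √(1 + 4/(n × 0.113))]² = (194.6/4) × [1 + √1.182]² = 211.9, so 212 (pooled: 215).

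So 195 is the uncorrected figure.

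**Step 3: dilute the control rate.** 

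Diluted rate = 0.146 + q × f × 0.113. Power = Φ(d / SE − 1.960), where d = 0.259 − diluted rate and SE = √{[0.259 × 0.741 + c(1 − c)] / 195}, with c the diluted rate.

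Worked example, q = 0.20 and f = 1: c = 0.146 + 0.0226 = 0.1686; d = 0.0904; SE = 0.0413; d/SE = 2.19; power = Φ(0.23) = 59.1%.

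| Added contamination | Control rate, full effect | Difference (points) | Power, full effect | Power, half effect |
|---|---|---|---|---|
| 0% | 14.6% | 11.3 | 80.1% | 80.1% |
| 5% | 15.2% | 10.7 | 75.4% | 77.8% |
| 10% | 15.7% | 10.2 | 70.3% | 75.4% |
| 15% | 16.3% | 9.6 | 64.8% | 72.9% |
| 20% | 16.9% | 9.0 | 59.1% | 70.3% |

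With pooled variance, the full-effect column becomes 79.5, 74.9, 69.8, 64.3 and 58.7%. The choice of variance moves the result by about half a point.

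**Step 4: the same with the stated correction.** At 195 per group, pooled variance and full effect, power is 75.7% at zero contamination and 70.7, 65.2, 59.6 and 53.8% at the four rates.

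**The case against.** Several objections have force and limit the point.

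- **The rates are not a forecast.** A reader might infer that the protocol expects 5 to 20% contamination, especially as zero is not listed. The text does not support this. The rates are hypothesized for a sensitivity analysis, and such a grid omits zero naturally because zero is the main analysis.
- **The loss does not follow from the protocol's figures alone.** A reader might take 75% to 59% as the trial's power on its own numbers. The article gives no quit rate for controls with access. Access is not the same as receiving a 12-week programme of 121 messages, so the full-effect column is the worst case at each rate. With half the effect, power is about 78% to 70%.
- **Some contamination may already be counted.** The 14.6% was observed in an earlier text-message trial with a delayed-intervention control group. By the protocol's own reasoning about eHealth trials, that arm may have been exposed to some degree. The excess in the new trial cannot be derived from the article.
- **195 analysed assumes the full 30% attrition.** If all 279 per group responded, power without correction would be about 88% to 74% over the four rates at full effect. The sizing does not rely on this.
- **The dilution is already disclosed**, with its direction, in the Randomization section. No slip in arithmetic is involved in leaving it out of the sizing.

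What remains is that the 80% is stated without condition, and that power falls below it at each of the four rates under either assumed effect.

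**Conclusion.** The point holds as one of transparency. The sizing makes no allowance for a dilution that the same article treats as unpreventable, so 80% describes only the case of no contamination beyond any already in the 14.6%. For added contamination of 5 to 20%, power at 195 analysed per group would be about 75% to 59% at full effect and about 78% to 70% at half effect, both without continuity correction. In the most adverse of these scenarios, a true 11.3-point benefit of the programme would be missed about 41% of the time (100 − 59) instead of 20%.

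A reader might go further and conclude that the trial is underpowered or must be enlarged. The documents do not support that: neither the actual contamination nor the effect of access is known.

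**What to change.** Keep 558. In the Power calculation section, state that 80% was computed without continuity correction and applies only with no contamination beyond any already in the earlier trial's 14.6%. Then add that, if a further 5, 10, 15 or 20% of controls had access, power at 195 analysed per group would be about 75, 70, 65 or 59% if they quit at the full intervention rate (worst case), or about 78, 75, 73 or 70% if they gained half the effect. Label these as assumption-based scenarios and refer to the Randomization section.

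Reconcile the words on continuity correction as a separate matter. If the correction is kept with 195 per group, the matching figures are about 76% at zero contamination and about 71, 65, 60 and 54% at the four rates with full effect.

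The cost is two or three sentences and a less favourable stated power. No participants are added, and neither the design nor the analysis changes.

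### The 195 per group is the sample size without the continuity correction the plan says it includes; with the correction, 212 to 215 are needed, and 195 gives about 76% power rather than 80%

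*Protocol article*

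**What the plan says.** The Power calculation section of the protocol article takes its rates from the sponsor's earlier trial among university students, where "25.9% reported prolonged abstinence in the intervention group" and "14.6% in the control group, i.e., an 11.3% difference between the two groups". The target is 80% power, with "significance level of 0.05 (two-sided) and correction for continuity". From these inputs the section states: "correction for continuity, a sample size of 195 persons is needed in each group". It then allows for 30% attrition, so that "the number needed in each group is 279, with a total required sample size of 558". The Design section specifies equal group sizes.

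The Data analysis section says that the binary outcomes, including both primary outcomes, "will be analyzed by logistic regression and the results presented as odds ratios and 95% confidence intervals (CIs"). It mentions no continuity correction for any test.

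**The concern.** Every input to the calculation is stated, so the 195 can be checked directly. A continuity correction always raises the required sample size, and at these rates the increase is about 17 per group. The figure 195 coincides with the result before that increase.

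If the correction was intended but not applied, the trial lacks the stated power under the stated method, and the attrition-inflated targets of 279 and 558 inherit the shortfall. If it was never intended, the numbers stand and the description of the method is wrong. In both cases a reader who repeats the calculation as described arrives at a different sample size.

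**Working it through.** **Inputs.** From the Power calculation section: p1 = 0.259, p2 = 0.146, difference d = 0.113, two-sided alpha 0.05 (z = 1.960), power 0.80 (z = 0.8416), attrition 30%. From the Design section: 1:1 allocation.

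**Step 1: reproduce 195 without a correction.**

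Unpooled variance:

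n = (1.960 + 0.8416)² × (0.259 × 0.741 + 0.146 × 0.854) / 0.113² = 7.849 × 0.3166 / 0.01277 = 194.6, which rounds up to **195**.

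Pooled variance under the null, with mean rate 0.2025:

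n = [1.960 × √(2 × 0.2025 × 0.7975) + 0.8416 × √0.3166]² / 0.113² = 197.4, which rounds up to 198.

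The arcsine formula gives 195.0. The plan's figure is therefore matched by two standard formulas, both without the correction.

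**Step 2: apply the continuity correction.** The usual adjustment is

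n_c = (n/4) × [1 + √(1 + 4/(n × d))]².

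- Unpooled: (194.6/4) × [1 + √(1 + 4/21.99)]² = 211.9, so **212**.
- Pooled: (197.4/4) × [1 + √(1 + 4/22.30)]² = 214.7, so **215**.
- Arcsine: 212.3, so 213.

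Relative to 195, this is 212/195 = 1.09 to 215/195 = 1.10.

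**Step 3: attrition.** 195/0.70 = 278.6, so 279 per group and 558 in total; the plan's attrition step is right. With the correction, 212/0.70 = 302.9, so 303 per group and 606 in total; 215/0.70 = 307.1, so 308 per group and 616 in total.

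**Step 4: power at 195 analysed per group.** In the normal approximation the correction reduces the difference by 1/n = 1/195 = 0.0051, to 0.1079. The exact figures sum the binomial probabilities of all outcomes that the test declares significant.

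| Method at 195 per group | No correction | With correction |
|---|---|---|
| Normal approximation, pooled | 79.5% | 75.7% |
| Normal approximation, unpooled | not computed | 76.3% |
| Exact, chi-square test | 80.0% | 76.1% |

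Exact enumeration of the likelihood-ratio test at 195 per group also gives 80.0%. Exact power of the corrected chi-square test is 79.7% at 212 per group and 80.4% at 215, which confirms 212 to 215 as the corrected requirement.

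**Step 5: look for another explanation of 195.**

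- *Sidedness:* a one-sided calculation (pooled) gives 156 without the correction and 173 with it.
- *Rounding of the rates:* the most favourable values that still round to the stated ones are 25.95% and 14.55%. They give a corrected unpooled requirement of 208.3, about 7% above 195.
- *A different control rate:* a corrected figure close to 195 appears only if the control rate is lowered to about 14% (193 per group, pooled). That contradicts the stated 14.6% and the stated difference of 11.3 percentage points.

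**The case against.** The strongest reply is that the 76% belongs to a test this trial will not run. The primary outcomes go to logistic regression, with no continuity correction, and at 195 per group both the uncorrected chi-square and the likelihood-ratio test have 80.0% power on the stated rates. On this view 195, 279 and 558 suit the planned analysis, and the fault is a misplaced phrase rather than an underpowered design. Had the correction been applied, it would only have made the sample size conservative: exact uncorrected power at 212 per group is about 83%.

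Most of this stands. It limits the practical consequence, and the 76% must be read as conditional on a corrected test. It does not make the sentence correct: the section names a method, and that method does not give the number reported.

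A second reservation also stands. The article names no formula or software. That 195 excludes the correction is well supported; whether it came from the unpooled formula, the arcsine formula or something else is inference, and the sponsor should confirm it.

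**Conclusion.** The concern holds. On the plan's own inputs, 195 per group is a sample size without a continuity correction, and the statement that it includes one is wrong. Under the stated method the shortfall is 17 to 20 analysed participants per group (212 − 195 and 215 − 195), or about 4 points of power. The totals of 279 and 558 are correct for an uncorrected calculation and too low for a corrected one.

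These figures assume 25.9% and 14.6% are the true rates and that 195 per group are actually analysed, that is, after the planned 30% attrition. They are for an unadjusted comparison of two proportions; the effect of the planned baseline covariates on power is not modelled. Because the planned analysis uses no correction, the design itself is close to its 80% target. What needs correcting is the reported basis for the sample size.

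**What to change.** Preferred: delete the reference to a continuity correction from the Power calculation section, state that the sample size comes from an uncorrected two-proportion calculation (naming the formula once the sponsor has confirmed it), and add that this agrees with the logistic-regression analysis. The figures 195, 279 and 558 then stay as they are.

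Alternative: keep the correction and state that 195 analysed per group gives about 76% power with it.

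Each option costs one sentence and no additional participants; the second also means reporting a slightly less favourable power.
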